## Abstract

**Background:**

South Africa is currently undergoing a nutrition transition, and overweight and obesity is on the increase in South African children. Urbanization and other health determinants have led to reduced physical activity and unhealthy eating that have increased the risk of adverse chronic health conditions. This study aims to provide evidence of the effectiveness of a school-based intervention study that targets diet and physical activity for the prevention of child and adolescent overweight and/or obesity.

**Methods:**

We will employ a mixed method study design which is divided into two phases. Phase 1, namely the qualitative elicitation research phase will inform the development of the quantitative intervention phase (phase 2), consisting of a cluster-randomized trial, based on input from key stakeholders. The study will be undertaken in 16 government-funded primary schools in the iLembe district of KwaZulu-Natal, South Africa. The study will target learners in Grades 4 and 7, their parents, Life Orientation educators, school principals and members of school governing bodies. Assessment for the primary objective (BMI Z scores), and the secondary objectives (change in knowledge, attitudes and behaviours regarding diet and physical activity) in both study arms will be conducted at baseline in March 2020 and at the end of the study in October 2020.

**Discussion:**

The study will be a novel combined mixed methods/RCT design that focuses on diet, physical activity school and family-based interventions in the context of rapidly increasing overweight and obesity prevalence in KwaZulu-Natal. To encourage behaviour change and management of malnutrition, education including diet and physical activity, is an important strategy that must be considered. Nutrition education extends beyond the dissemination of food information; it includes addressing the needs of participants, empowers and encourages decision-making and choice of foods, change in nutrition attitudes, beliefs and influences based on resources available and within cultural boundaries.

**Trial registration:**

Pan African Clinical Trial Registry PACTR201711002699153. Protocol registered on 16 November 2017.

## Background

Contributing to the over nutrition epidemic, an estimated 340 million children and adolescents aged 5–19 years were overweight or obese in 2016 [1]. The World Health Organization (WHO) global nutrition targets for 2025, especially target 4, has a specific focus on preventing an increase in childhood overweight [2]. The rapid increase in overweight and obesity in children and adolescents, largely due to modifiable risk factors such as unhealthy eating and physical inactivity, is strongly influenced by the physical environment, as well as cultural, social and economic factors [3]. It is estimated that by the year 2020, lifestyle-related non-communicable diseases (NCDs) will account for 60% of the burden of disease, and 70% of deaths worldwide, if adequate health promotion intervention programmes are not established. To reduce this chronic disease burden, modification of one’s lifestyle, promotion of prevention measures against NCDs and improved dietary habits and physical activity are important [4, 5]. Furthermore, a cause for public health concern is the increasing trend of child and adolescent weight gain as they transition into adulthood. Adolescents, 10–19 years of age, as defined by the WHO, are targeted for interventions as it is during this growth and development period that health attitudes, beliefs and behaviours are established and continue into adulthood [3]. The adolescent years have been referred to as the “tipping years” by Hanvey et al., [6], where co-morbidities such as high blood pressure, diabetes, stroke, cardiovascular disease and cancer may appear as short term health consequences [7].

In an effort to reverse and stop the increased trend of overweight and obesity, children should be brought up in a health promoting environment where instead of traditionally following the choices of others they can make informed choices about their health [3]. The school is viewed as an ideal health-promoting environment that can develop children and adolescents physically, emotionally and socially [8]. Literature on school obesity interventions exists, and while some literature that specifically focuses on diet and physical activity exists, such tend to focus on anthropometric measures such as body mass index (BMI) only, self-efficacy and some positive evaluations and outcomes [9–11]. In South Africa, there have been minimal obesity intervention studies, with some focusing on physical activity only, and nutrition interventions having either a food questionnaire to identify food choices or BMI measurements only. The HealthKick study, comprising of diet and physical activity interventions is the only known study in South Africa that aimed to address the prevention of overweight in children and reduce the risk of chronic diseases such as type 2 diabetes. This study identified significant improvement in self-efficacy and nutrition knowledge but not in children’s nutrition behaviour. Limitations of the study included lack of parent participation, as well as the authors suggesting that creating a healthier food environment within and around the school was important [12]. The study, in addition to other international studies, has been helpful in assisting in the development of the iLembe School Physical Activity and Nutrition (i-SPAN) study. The i-SPAN study identified the strength and weaknesses of South African studies and while these studies were implemented with some success in low-income areas, literature for school-based diet and physical activity interventions is still limited in the African setting [13–15].

Therefore, there is a need to develop and implement interventions that are specific for lifestyle diseases and conditions that target the child groups relevant to South Africa. Such interventions may be difficult to conduct and sustain due to a lack of funding and resources. Thus, the i-SPAN study has been developed and will be conducted in the poverty-challenged iLembe District in the province of KwaZulu-Natal in South Africa. The elicitation research phase will inform the development of an intervention phase that will design, implement and assess the effectiveness of school-based interventions that focus on diet and physical activity in children and adolescents in Grades 4 and 7 (aged 9–15 years). It is during these years that most girls (8–13 years) and boys (10–15 years) enter puberty, reaching a growth peak that results in a healthy BMI and weight [16].

### Trial aims and objectives

The aim of this cluster randomized controlled trial (RCT) is to provide evidence of the effectiveness of diet and physical activity interventions conducted in schools in preventing overweight and obesity in children and adolescents.

### Specific objectives

#### Phase one: elicitation research

To assess the health promotion status of children and adolescents in the iLembe district schools (what children know about diet and exercise, and their diet and physical activities), explore and understand the school children’s attitudes, cultural beliefs, vision and ideas regarding obesity, and identify the extent to which health promotion has been utilized in the schools regarding diet and physical activity.To identify facilitating and constraining factors for health promotion (diet and physical activity) in the schools in iLembe district according to the key stakeholders such as Department of Basic Education (DoBE), Department of Health (DoH), Department of Sports and Recreation and other stakeholders such as the Health Promotion Coordinators, District Nutrition Coordinator, School Health Teams.To design and implement diet and physical activity school-based interventions to reduce obesity in school children.

#### Phase two: intervention

4.To assess the effectiveness of the i-SPAN study in children and adolescents aged 9–15 years by comparing the intervention and control arms at baseline and at the end of the study regarding:
BMI Z scores.Proportion of children and adolescents classified as overweight and obese.Knowledge, attitude and behaviours regarding diet and physical activity.5.To describe and evaluate the outcomes of the interventions for scientific dissemination.

## Methods

The protocol has been developed using the Standard Protocol Items: Recommendations for Interventional Trials (SPIRIT) guidelines [17] (Additional file 1).

### Design

The study is a cluster randomized controlled trial, with both quantitative and qualitative components, to determine the effectiveness of the i-SPAN study to prevent overweight and/or obesity in children and adolescents (Fig. 1).

**Fig. 1 Fig1:**
[figure not shown]
Study design of the i-SPAN study

### Participants and recruitment process

The participants of the study will include children in grade four (aged 9-11 years) and grade seven (aged 12-15 years), as well as parents/primary caregivers, Life Orientation (LO) educators, principals, members of the community, the latter through the school governing body (SGB). When the data has been collected meetings will be held with the SGBs (from whom permission will be required prior to the study) to inform them of the results and get their input on the way forward. They will also be the link with the wider community. Other stakeholders will include DoBE, DoH, Sports and Recreation, Health Promotion Coordinators, the District Nutrition Coordinator and School Health Teams in iLembe district, KwaZulu-Natal. The study setting will be primary schools in iLembe district.

A complete list of all schools with grade four and seven children in iLembe district will be provided by the Provincial Department of Basic Education. The list includes over 400 primary schools from which 16 schools will be selected randomly with probability proportional to size (PPS). There will be four schools from each of the four sub-districts, which will be randomly assigned into the two study arms (control *n* = 8, intervention n = 8). Two schools will receive the intervention and two schools will serve as controls in each of the four sub-districts. All children and adolescents in grade four and seven attending these schools and their parents/primary caregiver will be invited to participate in the study. Children and adolescents must provide assent in writing via the consent forms. Parents/caregiver must also provide consent for participation in the study for the children/adolescents and themselves (Additional file 2). South African schools are arranged into quintiles determined by the National Treasury, based on scores reflective of the poverty levels where a community is situated. The DoBE uses these poverty classifications that range from quintiles 1–5, where quintile five is the least poverty-stricken and one is the most poverty-challenged quintile, to classify schools. Most of the primary schools in iLembe district are from quintiles 1 and 2, hence it is important to understand the daily challenges these communities face regarding housing, socio-economic status, employment, as well as health outcomes as these are regarded as schools with low socio-economic status and exempt from school fees [18].

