### Sample size/power calculation

The school is the unit of the study. The power/sample size calculation was performed using a test for two means in a cluster randomized design function implemented in PASS 12 [19]. A power calculation indicated that with 8 schools in each arm and 68 participants per cluster, the study would have 90% power (1-β) to detect an underlying medium standardized difference between the means (effect size) of 0.3 following the intervention, at a two-sided 5% significance level (α), assuming an intra-class correlation coefficient (ICC) of 0.05 or 5% [20, 21].

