### Randomization

The school is the unit of the study. A biostatistician who does not have direct contact with study participants will generate the random allocation sequences using a computerized random number generator. After the inclusion of each cluster, the allocation of that particular cluster will be provided to the study coordinator. There will be no crossover between study arms.

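### Schools are randomised within sub-district only; also balancing the 16 on poverty quintile and size, both knowable beforehand, would be a cheap improvement rather than the correction of an error

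*Protocol article*

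**What the plan says.** The section *Participants and recruitment process* draws 16 schools with probability proportional to size, four per sub-district. On allocation it states: "There will be four schools from each of the four sub-districts, which will be randomly assigned into the two study arms". It then fixes the split: "Two schools will receive the intervention and two schools will serve as controls in each of the four sub-districts". The section *Randomization* has a biostatistician generate the sequence by computer and adds: "After the inclusion of each cluster, the allocation of that particular cluster will be provided to the study coordinator". Sub-district is the only restriction named.

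The recruitment section also describes the official poverty quintile of each school and says: "Most of the primary schools in iLembe district are from quintiles 1 and 2, hence it is important to understand the daily challenges" of these communities, with health outcomes among the matters it lists.

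*Planned statistical analysis* describes mixed models with a school random effect, a check of baseline differences between arms, and change in BMI among the outcomes. It names no school-level covariate.

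**The concern.** Two school-level factors can be known before allocation and are not used in it. Size is required for the sampling draw. Quintile is already assigned to every school, and the protocol itself treats it as important. With only 8 schools per arm, a plain 2:2 draw in each sub-district can place the few better-off or largest schools mostly in one arm.

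If those factors are related to BMI Z score, the result is avoidable between-school noise in the arm contrast. It also leaves a baseline table that invites doubt about the comparison. Checking baseline differences after allocation can reveal such an imbalance but cannot prevent it. A lopsided size split also makes the arms unequal in number, because all Grade 4 and 7 learners in a selected school are invited.

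**Working it through.** **Inputs from the article** (*Sample size/power calculation*; *Participants and recruitment process*): 8 schools per arm, 68 learners per school, ICC 0.05, two-sided 5% level, and a "medium standardized difference between the means (effect size) of 0.3 following the intervention". Four sub-districts, 2:2 in each.

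**Inputs not in the article (assumptions):** how the 16 schools fall by quintile; the quintile gap in the outcome, taken as 0.2-0.3 SD; the share R² of between-school variance that quintile and size explain.

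**1. The plan's own figure.** Design effect = 1 + 67 × 0.05 = 4.35. Effective number per arm = 8 × 68 / 4.35 = 125.06. Power for 0.3 SD is 66.0% (normal) or 59.8% (t, 14 df), not the stated 90%. That discrepancy is a separate matter; here 66.0% / 59.8% only serves as the baseline for step 6.

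**2. Room for chance.** Permitted allocations: C(4,2)⁴ = 6⁴ = 1,296. With total SD = 1, the whole between-school component of a follow-up contrast has SD √(0.05 × 2/8) = 0.112.

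**3. Splits of a binary school factor (full enumeration).**
- One differing school per sub-district: 0/1/2/3/4 of them fall in the intervention arm in 81/324/486/324/81 draws. So 37.5% of draws are 2:2, 50% are 3:1 and 12.5% are 4:0.
- Two per sub-district: the counts are the coefficients of (1 + 4x + x²)⁴, namely 1, 16, 100, 304, 454, 304, 100, 16, 1. Splits of 6:2 or worse occur in 2 × (100 + 16 + 1) = 234 draws, or 18.1%.
- Every sub-district homogeneous: no imbalance is possible.

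**4. Shift in a follow-up-only contrast** = (difference in counts / 8) × gap.

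| Split | Gap 0.2 SD | Gap 0.3 SD |
|---|---|---|
| 3:1 | 2/8 × 0.2 = 0.05 | 2/8 × 0.3 = 0.075 |
| 4:0 or 6:2 | 4/8 × 0.2 = 0.10 | 4/8 × 0.3 = 0.15 |

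**5. Are these gaps compatible with the ICC?** A binary factor present in a share p of schools has variance p(1−p) × gap², to be compared with 0.05.

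| Gap | 4 of 16 schools | 8 of 16 schools |
|---|---|---|
| 0.2 SD | 0.0075 (15%) | 0.0100 (20%) |
| 0.3 SD | 0.0169 (34%) | 0.0225 (45%) |
| 0.5 SD | 0.0469 (94%) | 0.0625 (125%) |

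A gap of 0.5 SD would use almost all, or more than all, of the between-school variance that the plan assumes, so it is left out. Even 0.3 SD is generous.

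**6. What balancing could gain.** If quintile and size explain a share R² of the between-school variance and the analysis accounts for them, power at the stated inputs becomes:

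| R² | Normal | t, 12 df |
|---|---|---|
| none removed | 66.0% | 59.8% (14 df) |
| 0.10 | 69.5% | 62.2% |
| 0.25 | 75.3% | 68.1% |
| 0.50 | 86.0% | 79.7% |

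The article gives no value for R², so no row can be singled out.

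**The case against.** The case against is strong, and most of it stands.

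- Stratified 2:2 randomisation of 16 clusters is a valid design. Chance imbalance on quintile or size is part of the between-school variance that the ICC and the school random effect already cover. It is not bias.
- BMI Z score is measured in both arms at baseline and at the end of the study, and change in BMI is a named outcome. A stable quintile gap in level largely cancels in a change contrast; only a quintile difference in change between March and October 2020 would remain. The shifts in step 4 are therefore upper figures for their scenarios.
- Most schools in the district are in quintiles 1 and 2, so the spread is narrow, and sub-district stratification may already absorb part of it.
- No size distribution is given, and neither quintile nor size is linked numerically to BMI Z score. The size component cannot be quantified at all.
- The covariate list may sit in an analysis plan that is not shown, so its absence from the article is no finding.

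A reader might infer that this allocation can move the contrast by up to half the planned effect, or that it biases the trial. The document supports neither. Half the planned effect (0.15 SD) comes from an assumed gap and an assumed mix of schools. It is not a maximum even under those assumptions: with two better-off schools per sub-district, an 8:0 split is possible. Under other mixes the shift is zero.

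What survives is narrower. The allocation scheme is stated in this article, it makes no use of two factors available beforehand, and it cannot be repaired once schools have been allocated.

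**Conclusion.** This is an optional but worthwhile improvement, not an error. Sub-district is the only restriction on allocation, and with 8 schools per arm a lopsided split on quintile is not rare under plausible mixes: 12.5% of draws at 4:0 with one better-off school per sub-district, or 18.1% at 6:2 or worse with two. Those percentages are exact given the assumed mix. Their translation into 0.10-0.15 SD (for 4:0 or 6:2) rests on an assumed gap of 0.2-0.3 SD and a follow-up-only comparison, and a pre/post change contrast would move less. What is at stake is precision and face credibility. The amount cannot be determined from the document.

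**What to change.** 1. Identify all 16 selected schools before any is allocated, and amend *Randomization*, which now releases allocations school by school.
2. List the 1,296 permitted 2:2 allocations and keep those balanced on quintile and on mean Grade 4 plus 7 enrolment. Choose a quintile cut that actually divides the selected schools, such as quintile 1 versus 2 and above; a cut at 1-2 versus 3-5 may leave little to balance.
3. Check that the retained set is not over-constrained: it should stay large, and no pair of schools should be forced always together or always apart beyond what the 2:2 rule implies. Exact balance on quintile alone would keep 486 allocations (one differing school per sub-district) or 454 (two); enrolment reduces this further.
4. Have the biostatistician draw one allocation at random from the retained set.
5. Reflect the balancing in the analysis, either by adjusting for the balancing factors or by a permutation test over the retained set. Otherwise the standard error will not show the gain.

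Cost: a short allocation program and a few protocol sentences, with no extra schools or learners. Allocation has to wait until all schools are identified, Grade 4 plus 7 enrolment must be on hand for each, and one or two school-level degrees of freedom are spent if the factors are modelled.

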### Planned statistical analysis

#### Descriptive and analytical statistics

The use of weight and height, BMI calculations, completed questionnaires, arising from the interventions will use both descriptive and inferential statistics to analyse the data. To ensure succession of cluster randomization, the presence of any significant differences between the control and intervention cluster for the baseline characteristics of the participants such as sex, age, etc., will be examined using bivariate mixed effect regressions to account sufficiently for the clustered design. Data will be processed and analysed using Stata 13.0 SE. Mixed effects using generalized linear and logistic modelling approaches will be used to compare continuous and binary endpoints respectively among students in schools in intervention and control arms of the study. A within school random effect will be incorporated to account for correlated (repeated) measurements within each school to correctly estimate the significance when comparing pre- and post-intervention periods. Outcome variables include change in BMI at baseline and end of study, dietary intake, time spent in sedentary behaviours, diet and physical activity self-perception and practices, including overall knowledge and attitude regarding diet and physical activity- significant levels and stratified analyses.

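### Schools are allocated two per arm within each sub-district, but the stated model carries only a school random effect; the cost ranges from nil to substantial

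*Protocol article*

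**What the plan says.** Under Participants and recruitment process the protocol article describes a restricted allocation: "There will be four schools from each of the four sub-districts, which will be randomly assigned into the two study arms", and then "Two schools will receive the intervention and two schools will serve as controls in each of the four sub-districts". The Randomization section does not repeat the restriction, but nothing in it conflicts with it.

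Under Planned statistical analysis, the arms are to be compared by mixed linear models for continuous endpoints and mixed logistic models for binary ones. For clustering, "A within school random effect will be incorporated", with the stated purpose of getting the significance right when the pre- and post-intervention periods are compared. Sub-district is not named as a fixed effect, a random effect or a stratum. The paragraph closes with a mention of stratified analyses but does not say by what.

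The Sample size/power calculation section treats the design as an unstratified two-arm cluster comparison "with 8 schools in each arm and 68 participants per cluster" and gives no variance between sub-districts.

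**The concern.** Two schools per arm in every sub-district means that a difference between sub-districts contributes equally to both arms and drops out of the arm contrast. A model with a school random effect and no sub-district term does not know this. It leaves the sub-district differences in the between-school variance and so in the standard error. In randomisation terms, the design allows 6 × 6 × 6 × 6 = 1,296 allocations, whereas the model behaves as if all 12,870 ways of splitting 16 schools into 8 and 8 were possible.

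Between-school variance is the main source of error here. If sub-districts do differ, the trial gives up precision that its own allocation has already secured.

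**Working it through.** **Inputs** (Sample size/power calculation): 8 schools per arm, 68 children per school, standardised difference 0.3, ICC 0.05, two-sided 5%. **Assumption**: a share *s* of the between-school variance lies between sub-districts. The article gives no value, so *s* is varied from 0 to 0.7.

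**1. The article's own power figure.** Design effect = 1 + 67 × 0.05 = 4.35. Effective n per arm = 544 / 4.35 = 125.06. SE = √(2 / 125.06) = 0.1265, and 0.3 / 0.1265 = 2.37. Power is 66.0% (normal) or 59.8% (t, 14 df). The stated 90% does not reproduce. That is a separate matter, but it explains why the powers below start near 60%.

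**2. Mechanism.** The variance of a school mean is 0.05 between schools plus 0.95 / 68 = 0.0140 within.

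- Actual variance of the arm contrast: [0.05(1 − *s*) + 0.0140] / 4.
- Expected estimate without sub-district: [0.05(1 − *s*) + 0.0140 + (6/7) × 0.05*s*] / 4. The factor 6/7 arises because each arm has 8 schools in 4 pairs: 2 × 3 = 6 units of sub-district variance spread over 7 df.

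At *s* = 0.30 the actual SE is √(0.0490 / 4) = 0.111. The expected reported variance is (0.0490 + 0.0129) / 4 = 0.0155, so the root-mean-square reported SE is about 0.124.

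**3. Degrees of freedom.** Without sub-district: 16 − 2 = 14, critical t 2.145. With it: 16 − 4 − 1 = 11, critical t 2.201.

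**4. Break-even.** Equate the squared half-widths. With c = (2.201 / 2.145)² − 1 = 0.0531,

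*s* = c × 0.0640 / (0.05 × 6/7 + 0.05c) = 0.00340 / 0.0455 ≈ 7.5%.

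**5. Simulation.** 200,000 trials per setting, school means at one time point, t-based tests; *unadj.* is without sub-district, *adj.* with it as a fixed effect.

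| Share *s* (assumed) | CI width, unadj. / adj. | Type I error, unadj. | Power, unadj. | Power, adj. |
|---|---|---|---|---|
| 0% | 0.98 | 5.0% | 59.7% | 58.0% |
| 5% | 1.00 | 4.6% | 60.2% | 59.8% |
| 10% | 1.01 | 4.3% | 60.5% | 61.4% |
| 20% | 1.05 | 3.9% | 61.6% | 65.3% |
| 30% | 1.10 | 3.2% | 62.4% | 69.5% |
| 50% | 1.21 | 2.2% | 65.0% | 78.9% |
| 70% | 1.38 | 1.4% | 68.1% | 89.3% |

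The adjusted t-test holds its type I error at about 5% throughout.

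**6. Normal cut-off (1.96) instead of t.** Type I error without sub-district is 7.0% at *s* = 0, 6.2% at 10%, 5.6% at 20%, 4.7% at 30% and 3.4% at 50%. The intervals are therefore too narrow until *s* reaches roughly 25 to 30%. With sub-district in the model but still a normal cut-off, type I error is 7.5% to 7.8% throughout, so the sub-district term is not enough without the small-sample df.

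**The case against.** The article is condensed, and a covariate list is the kind of detail often left to a fuller plan. The analysis section lists no covariates at all, does not say that the school effect is the only term, and mentions stratified analyses. This stands in part: a reader might infer that sub-district has been deliberately excluded, and the text does not show that. But the article does state the model family, the clustering term and its purpose, and that structure does not match the allocation it describes. A mention of stratified analyses with no stratum named does not fill the gap.

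The consequence is also conditional. A reader might infer that the intervals will be too wide and power will be lost. The article does not support that as a fact. It gives no sub-district variance; all schools lie in one district and most primary schools there are in the two poorest quintiles, so a small share is plausible. It also names no reference distribution, and under a normal one the error can go the other way.

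Finally, the simulation uses one time point, whereas the article plans pre/post comparisons and lists change in BMI as an outcome. Sub-district differences that persist from March to October largely cancel in a change. The relevant share is then that of the variance in change, which may be much smaller. This stands: the 30% and 50% rows are illustrations and cannot be carried over to a pre/post model.

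**Conclusion.** The point holds in conditional form. The allocation is balanced within sub-district and the model as described does not account for it. If sub-districts differ in the outcome actually analysed (end-of-study value or change), t-based inference is conservative and power is lost.

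Under the single-time-point assumptions, including sub-district changes power by about −2 points at a share of 0%, +1 at 10%, +7 at 30% and +14 at 50%. The treatment estimate is not biased either way. What favours acting is the asymmetry: the most it can cost is about 2 points, and the gain can be several times that.

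This adjustment should not be read as a repair of the stated 90% power. On these inputs it would come close (89.3%) only if sub-districts accounted for about 70% of the between-school variance.

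**What to change.** Add to Planned statistical analysis that sub-district, the allocation stratum, enters the between-arm models as a fixed effect with 3 df, in a form that acts on the arm contrast:

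- in a baseline-adjusted model of the end-of-study value, as a main effect;
- in a pre/post model, as sub-district by period, since a main effect alone adjusts only the level and not the change.

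For the continuous primary outcome, state small-sample inference with about 11 school-level df. For the binary endpoints, include the same term; the figures above do not cover logistic models, so their small-sample method should be stated separately. If a fuller plan already does this, a clarifying phrase in the article is enough.

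The cost is a line or two of text and 3 df (critical t 2.20 instead of 2.14), or about 2 power points if sub-districts do not differ. Data collection is unchanged.
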